#### Outcomes for assessment of effectiveness

We will calculate baseline to 6-month changes in outcome variables outlined in table 3. In a potential future trial, the primary outcome measure will be change in weight from baseline to 6 months. Other measures of interest include health-related quality of life (HRQOL) and well-being, economic impact (health resource use, out-of-pocket expenses) and psychosocial factors hypothesised to be determinants of weight loss maintenance that are targeted by the intervention (disinhibition, food cravings, psychological flexibility).

**Table 3 T3:** Outcomes and measures

Domain	Outcome	Measure	Time point
Clinical outcomes	Height	Self-measured	0 months
	Weight	Self-measured	0 months; 6 months
Quality of life and well-being	Health-related quality of life	EQ-5D-5L^19^	0 months; 6 months
	Capability/well-being	ICECAP-A^20^	0 months; 6 months
Economic evaluation	Health/social care use	Bespoke resource use questionnaire	0 months; 6 months
	Out of pocket costs	Bespoke resource use questionnaire	0 months; 6 months
Psychosocial factors	Disinhibition	Three-Factor Eating Questionnaire^18^	0 months; 6 months
	Psychological Flexibility	Acceptance and Action Questionnaires (Weight related; food related)^21 22^	0 months; 6 months
	Depression Anxiety Stress	Patient Health Questionnaire 8-item^23 24^ Generalised Anxiety Disorder 7-item scale^25^ Perceived Stress Scale^26 27^	0 months; 6 months
	Habits	Bespoke questionnaire adapted from the Self-Report Habit Index^28^	0 months; 6 months

### Measurements and data collection

#### Visit schedule

Participants will be asked to complete online assessments at baseline and 6 months. Details of which measures will be taken at each appointment are summarised in table 4. Participants will be given an honorarium for completing online assessments (£10 for baseline and £20 for the 6-month assessment). Honoraria for assessment attendance are not dependent on intervention attendance or completion. Participants who complete qualitative interviews will be given a £10 honorarium per interview.

**Table 4 T4:** Schedule of enrolment, interventions and assessments

	Time point		
	Enrolment	Baseline (0 months)	Follow-up (6 months)
Enrolment			
Telephone eligibility screen	X		
Informed consent		X	
Randomisation		X	
Interventions			
Supporting weight maintenance			
Standard care		X	
Assessments			
Height		X	
Weight		X	X
Self-report questionnaires		X	X

#### Anthropometric measures

All outcomes will be assessed via online self-report questionnaires. Participants will be asked to measure and report their height and to weigh themselves on the day that they complete the outcome assessment so that they can report a self-measured weight. Instructions for self-measuring will be provided to reduce measurement bias.

#### Self-report questionnaires

Participants will complete a demographics questionnaire at baseline based on Progress-Plus^9^ factors (place of residency, race/ethnicity, occupation, gender/sex, religion, education, socioeconomic status, social capital, age, disability, relationship status, caring responsibilities, car ownership and access to the internet). Self-reported behavioural and psychosocial measures will be collected via validated self-report questionnaires, which will be completed online (table 3).

#### Referral data

Data on invited numbers and referrals will be gathered from the recruiting weight management programmes, where possible. Individual strategies to gather these data will be agreed with the weight management/referral service at set-up.

### Data analysis

#### Statistical analysis

Quantitative analyses will be primarily descriptive. We will describe the number and proportion of participants who are invited to the study, respond, enrol (by recruitment method) and complete outcome assessments. Each of these will be examined for potential biases by gender, age, ethnicity and socioeconomic status. Change from baseline to 6 months for weight and each of the secondary outcomes will be summarised separately within the intervention and standard care groups using mean (SD) or median (IQR). Linear regression will estimate the difference (intervention minus standard care) in mean change in weight from baseline, adjusted for baseline weight and the randomisation stratifiers (diabetes status and sex). Since this is a feasibility study, it is not powered to detect differences between randomised groups or mediation by psychosocial variables. However, it will provide estimates of the SD of weight at baseline and correlation between weight at baseline and weight at 6 months, which will inform the sample size calculation for a full-scale trial.

VOI methods will estimate the decision uncertainty associated with the intervention’s cost-effectiveness given the existing evidence base, and will determine the value of a definitive trial, based on ability to reduce decision uncertainty. Using data from the feasibility study, we will undertake a formal, structured elicitation process to elicit expected trial outcomes and uncertainty. We will use the Sheffield Elicitation Framework methods^10^ and recruit participant experts on the likely effectiveness of the intervention from within the research team and externally. If the elicitation suggests very small effects and a high cost then we might already be certain of poor cost-effectiveness. If it suggests large effects and a small cost, this may be sufficient to suggest the intervention is highly cost-effective. However, and most likely, if the intervention lies somewhere between these scenarios, we will use expected value of sample information to estimate the value of alternative trial designs in reducing uncertainty in the cost-effectiveness estimates. This will help to select an optimal trial design to inform future cost-effectiveness analyses. We currently plan to examine three options for sample size (small, medium, large) and follow-up (1.5, 3, and 5 years), however, the exact details will be developed in an iterative process to support the trial design.

#### Economic analysis

Economic analyses (cost-effectiveness analysis, cost–utility analysis) will be undertaken, comparing the incremental costs and effects of the SWiM programme versus standard care. We will conduct a microcosting to estimate resource use for the set-up, delivery and maintenance of the SWiM programme. Resource use estimates will be derived from the literature and informed by feasibility study data, and will be adjusted based on expert input through an informal panel process.

Healthcare costs will be calculated as the product of resources used and appropriate unit costs adopting National Health Service (NHS) and personal social service (NHS-PSS) and patientperspectives. Cost components will include the SWiM intervention, primary care (eg, General Practitioner (GP) and nurse visits) and secondary care services (eg, outpatient and hospital admissions). Resource use data will be captured by case report forms (CRF) and a Short Health Economics Questionnaire (SHEQ), the latter also including over-the-counter medications, private visits, travelling and productivity loss. The CRF and SHEQ will be completed at baseline (covering the 3 months before the baseline) and 6 months (covering the 6 months from the baseline) by clinical personnel and patients, respectively. The outcomes used in the cost-effectiveness analysis will be the change in weight over time and HRQOL captured by the EuroQol EQ-5D-5L questionnaire, which will be expressed in quality-adjusted life-years.^11^ Missing data on costs and outcomes are anticipated, and will be handled using multiple imputation methods.^12^

Imputed mean cost-effectiveness in each arm will be used to obtain an incremental cost-effectiveness ratio (ICER), which will be calculated by dividing the mean cost difference by the mean effectiveness difference. These mean differences will be estimated using regression methods adjusting for HRQOL, costs and any unbalanced variables observed at randomisation. The uncertainty around the incremental cost and incremental effectiveness estimates will be evaluated using non-parametric bootstrapping methods and presented as cost-effectiveness probabilities, estimated as the proportion of the bootstrapped cost and effectiveness pairs with corresponding ICERs below different values of the cost-effectiveness threshold.

The economic analysis will also have a feasibility component. This will address whether any important cost components should be added to the analysis, the sources of unit cost data, the extent of missing data and methods for dealing with this, and the feasibility of all analytical methods. Second, the results of the probabilistic sensitivity analyses will be combined with the epidemiological information on projected numbers to undertake a VOI analysis to evaluate the potential economic value and acceptability of future research.^13^

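### Resource use and costs cover 3 months at baseline and 6 months at follow-up, so the planned within-arm change from baseline, taken on raw totals, shows unchanged use as a doubling

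*Protocol article*

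**What the plan says.** Three statements in the protocol article bear on this point.

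- **Recall windows (Economic analysis).** Resource use is captured on case report forms (CRF) and a Short Health Economics Questionnaire (SHEQ), which are "completed at baseline (covering the 3 months before the baseline) and 6 months (covering the 6 months from the baseline".
- **Change calculation (Outcomes for assessment of effectiveness).** "We will calculate baseline to 6-month changes in outcome variables outlined in table 3". Table 3 lists health/social care use and out-of-pocket costs at 0 and 6 months, both measured by a "Bespoke resource use questionnaire". The text above the table names "economic impact (health resource use, out-of-pocket expenses") among the measures of interest.
- **Reporting (Statistical analysis).** "Change from baseline to 6 months for weight and each of the secondary outcomes will be summarised separately within the intervention and standard care groups", as mean (SD) or median (IQR).

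For the comparison of costs between arms, the Economic analysis section has its own rule: "These mean differences will be estimated using regression methods adjusting for HRQOL, costs and any unbalanced variables observed at randomisation".

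The article does not say that resource-use totals are converted to a common period, and it does not exempt them from the change calculation.

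**The concern.** Weight, EQ-5D-5L and the psychosocial scales describe a state at the time of measurement, so follow-up minus baseline has a plain meaning. Resource use and costs are totals accumulated over a window, and here the follow-up window is twice as long as the baseline window. Subtracting one total from the other compares unlike quantities.

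The stake is descriptive. One listed objective of the study is to describe changes in outcome variables and estimate their variance for the design of a full-scale trial. For these two Table 3 items, the described change would largely reflect the length of the recall window, in both arms. Its SD would not be the SD of any change in use.

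**Working it through.** **Inputs.** Baseline window 3 months and follow-up window 6 months (Economic analysis). Change is planned for Table 3 variables measured at both times (Outcomes for assessment of effectiveness) and summarised by arm (Statistical analysis). The article gives no figure on this point to reproduce. The monthly rates below are illustrative assumptions, and the ratios do not depend on them.

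**Mean change on raw totals.** Let r be the monthly rate before baseline and k × r the monthly rate afterwards.

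- Baseline total = 3r. Follow-up total = 6kr. Raw change = 6kr − 3r. Ratio of follow-up to baseline = 2k.

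| True change in monthly use | k | Baseline | Follow-up | Raw change | Apparent change |
|---|---|---|---|---|---|
| None | 1 | 3r | 6r | +3r | +100% |
| 25% fall | 0.75 | 3r | 4.5r | +1.5r | +50% |
| 50% fall | 0.5 | 3r | 3r | 0 | 0% |

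Example: a steady £50 per month gives £150 at baseline and £300 at follow-up, a reported change of +£150 per person with no change in use.

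**On a common scale.** Per month, unchanged use gives 6r/6 − 3r/3 = 0. Doubling the baseline total to a 6-month equivalent gives 6r − 2 × 3r = 0.

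**SD of change.** Let B and F be the raw totals.

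- Raw: Var(F − B) = Var(F) + Var(B) − 2Cov(F, B).
- Per month: Var(F/6 − B/3) = [Var(F) + 4Var(B) − 4Cov(F, B)]/36.

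The second is not a multiple of the first, so a reader given only the SD of the raw change cannot recover the SD of the monthly change. In the limiting case where each person has their own constant rate, the monthly change is zero for everyone (SD 0), while the raw change is 3r per person with SD 3 × SD(r).

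**Between-arm comparison.** In F = a + βT + γB, where T is arm, replacing B by 2B halves γ and leaves β as it was. The baseline window therefore does not matter for a linear covariate. A simulation of 4,000 trials (40 against 20 participants, assumed mean 0.5 contacts per month, rate unchanged, no arm effect) agreed:

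- mean within-arm raw change: +1.50 contacts (expected 3 × 0.5 = 1.5);
- mean between-arm difference: about −0.01, both for raw change and for baseline-adjusted follow-up;
- largest difference in the adjusted estimate after rescaling the baseline: below 1e-14.

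**The case against.** The strongest reply is that the article never says raw totals will be subtracted. Both windows are stated openly, an analyst could convert to monthly rates, and the Programme steering committee section refers to a statistical analysis plan that may say so. This lowers the severity but does not remove the point. The article fixes unequal windows and fixes a change calculation over the same items, and the two do not fit together as written.

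A second reply is that the sentence about Table 3 is generic and cannot be read item by item, because the table also contains height. Height is listed at 0 months only, so no change can be calculated for it. Resource use and out-of-pocket costs are listed at both times.

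A third is that the windows are stated for the CRF and SHEQ, whereas Table 3 names a bespoke questionnaire. The SHEQ's content (over-the-counter medicines, private visits, travel) matches Table 3's out-of-pocket costs, so one dataset is the natural reading. It remains an inference, and the names need reconciling in any case.

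The limits on the consequences stand in full. A reader might infer that the cost-effectiveness result is distorted, or that the cost comparison under-corrects for baseline imbalance. The documents support neither. Both arms share the same windows, costs are compared by regression adjusting for costs, and no between-arm change score is planned for costs; the only such model is for weight. A reader might also infer that the future trial's sample size is at risk. The Statistical analysis section names only weight inputs for that purpose: its baseline SD and its correlation between baseline and 6 months.

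**Conclusion.** The point holds for the within-arm descriptive summaries of health/social care use and out-of-pocket costs. Calculated on raw totals, their change from baseline is inflated by exactly one baseline total when use is constant (+100%), and its SD has no usable interpretation. The stated objective of describing change and variance is not met for these items.

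The between-arm cost difference and the ICER are not affected. In a 60-person feasibility study whose quantitative analysis is mainly descriptive, this is a minor-to-moderate correction.

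The conclusion rests on three assumptions: change is taken on unconverted totals, the Table 3 questionnaire and the CRF/SHEQ capture the same data, and the cost adjustment in the regression means baseline cost entered as a linear covariate.

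**What to change.** Add one sentence to the analysis text, choosing one of two rules:

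- resource use and costs are expressed per month, or rescaled to one common period, before any change from baseline or its SD is calculated; or
- these items are exempt from the change summaries, and each period is reported separately with its length stated.

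Also use one name for the resource-use instrument in Table 3 and the Economic analysis section, or state how the bespoke questionnaire relates to the CRF and SHEQ and which recall window applies to each.

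Neither rule needs new data or a change to the forms. The planned between-arm cost regression can stay as it is.

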## Methods and analysis

This is a pragmatic, randomised, single-blind, parallel group, two-arm, feasibility study with an embedded process evaluation (figure 1). Participants will be randomised to either the ACT-based weight maintenance intervention (SWiM) or to standard care, using a computer-generated sequence with 2:1 allocation stratified by diabetes status and sex. This allocation will allow us to observe a reasonable number in the standard care group to gain information about their experiences, estimate retention in this group and assess willingness to be randomised. Participants will complete baseline and 6-month (from baseline) measurement sessions using online questionnaires. A subsample of participants from the standard care and intervention groups, and all coaches, will be invited to participate in qualitative interviews at both 3 months (mid-intervention) and 6 months from baseline (post-intervention). In addition, a subsample of participants who enrol but withdraw from the intervention group will also be interviewed. Qualitative interviews will collect data that will be used to contribute to both the feasibility evaluation and the process evaluation.

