### Participants

We will recruit adults (N=60) who have recently completed a behavioural weight loss programme lasting at least 3 months. Eligible participants will be recruited through NHS, local authority and commercial weight management services and diabetes prevention programmes in the UK, opportunistically, by referral and by mail out.

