### Randomisation

Participants will be allocated to one of the two intervention arms in a 2:1 allocation using block randomisation stratified by type 2 diabetes status and sex (male, female). The randomisation sequence will be computer generated by the trial statistician and programmed by the data manager. The sequence will be unknown to all other personnel, including study coordinators, outcome assessors and investigators. Once eligibility is confirmed and the online baseline assessment complete, the randomised allocation will be revealed to the participant by phone or email by the study coordinator. Intervention materials will then be provided depending on the group allocation. For logistical reasons, the study coordinator and the data manager will not be blinded to the allocation group. The trial statistician and the Investigators will be blinded to intervention allocation until the database is locked and the primary analysis complete.

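### The economic regressions choose covariates by observed baseline imbalance and do not name the stratification factors that the weight analysis fixes

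*Protocol article*

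**What the plan says.** Under Economic analysis, the mean cost and effect differences that form the ICER come from regressions "adjusting for HRQOL, costs and any unbalanced variables observed at randomisation". The section gives no candidate list and no criterion for imbalance, and it names neither diabetes status, sex nor baseline weight.

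The Randomisation and Methods and analysis sections describe allocation "using a computer-generated sequence with 2:1 allocation stratified by diabetes status and sex". Under Statistical analysis, the regression for weight change is "adjusted for baseline weight and the randomisation stratifiers (diabetes status and sex").

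Weight change is also an economic outcome: "The outcomes used in the cost-effectiveness analysis will be the change in weight over time and HRQOL captured by the EuroQol EQ-5D-5L questionnaire". The Statistical analysis section adds that, as a feasibility study, "it is not powered to detect differences between randomised groups".

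**The concern.** Under randomisation, any baseline difference between arms is chance. Its size says nothing about whether the variable predicts cost, QALYs or weight, and prediction is the reason to adjust. A rule based on observed imbalance therefore leaves the model open until the baseline table is seen, and two analysts following the same sentence could fit different models.

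The rule also works against the design. Diabetes status and sex are balanced by construction, so an imbalance rule will pass them over, although they are the two variables that the randomisation gives a reason to include. The weight difference in the ICER then need not equal the one reported under Statistical analysis.

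At stake are the incremental estimates and their spread. These go into the bootstrapped cost-effectiveness probabilities and, through the uncertainty analysis, may inform the value-of-information work.

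**Working it through.** The protocol gives no SD, power or derivation for the 60 participants, so there is no figure of its own to reproduce. The inputs taken from it are N = 60, 2:1 allocation (40 v 20), stratification by diabetes status and sex, and the two covariate statements. Everything marked as assumed below is not in the protocol.

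**1. The two adjustment sets for weight change**

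| | Statistical analysis | Economic analysis |
|---|---|---|
| Baseline weight | fixed | not named |
| Diabetes status, sex | fixed | not named |
| HRQOL, costs | no | yes |
| Unbalanced variables | no | yes, criterion not given |

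**2. How much the model depends on the threshold**

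The standard error of a standardised mean difference (SMD) at 40 v 20 is √(1/40 + 1/20) = 0.274.

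- P(|SMD| > 0.2) = 2[1 − Φ(0.2/0.274)] = 0.465.
- P(|SMD| > 0.25) = 2[1 − Φ(0.25/0.274)] = 0.361.
- The protocol lists 14 PROGRESS-Plus factors, 13 besides sex. If those 13 were the candidates (assumed), the expected number flagged is 13 × 0.465 ≈ 6.0 at |SMD| > 0.2, but 13 × 0.05 = 0.65 at p<0.05.
- The chance of at least one flag at p<0.05, treating candidates as independent, is 1 − 0.95^13 = 0.49; with 20 candidates it is 1 − 0.95^20 = 0.64.

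**3. Whether the rule selects the strata**

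The simulation used 4,000 trials per scenario. Assumed: blocks of 6 within diabetes × sex, 30% prevalence of each factor, 10 other covariates. A stratifier was flagged in 0% of trials at p<0.05 and in 1.0% to 1.5% at |SMD| > 0.25. An unstratified variable exceeds 0.25 in 36%.

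**4. Cost of leaving the strata out**

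Assumed: outcome SD 1, baseline value explaining 0.3 of variance, strata explaining r. The reported SE is about 0.274 × √0.7 without the strata and 0.274 × √(0.7 − r) with them, so the ratio is √(0.7/(0.7 − r)). The simulated figures agree:

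| r | Ratio by formula | Reported SE, without / with | True SE, without / with |
|---|---|---|---|
| 0.05 | 1.04 | 0.230 / 0.222 | 0.224 / 0.224 |
| 0.10 | 1.08 | 0.230 / 0.213 | 0.218 / 0.216 |
| 0.20 | 1.18 | 0.231 / 0.195 | 0.203 / 0.199 |

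Across all scenarios with r of 0.05 to 0.20, the true SE changed by 0% to 4% (largest: 0.204 v 0.197). Stratified allocation has already removed most of the variation due to the strata, so the loss is mainly an overstated reported SE. Bias was at most 0.006 outcome SDs throughout. Type I error under the imbalance rule was 0.015 to 0.043 when the strata were prognostic (conservative) and about 0.04 to 0.05 when they were not.

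**5. Effect of imbalance selection on the true spread**

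Assumed: 32 v 16 completers, baseline correlation 0.6, runs of 3,000 to 6,000 trials. The figures are changes in the SD of the estimate against adjustment for baseline only.

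| Threshold | Covariates | 13 candidates | 20 candidates |
|---|---|---|---|
| p<0.05 | pure noise | +4% to +5% | +6% to +7% |
| \|SMD\| > 0.2 | pure noise | +13% to +15% | +22% to +27% |
| p<0.05 | joint R² 0.2 | −1% | +4% |
| \|SMD\| > 0.2 | joint R² 0.2 | −3% | +6% |

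With 5 prognostic candidates and |SMD| > 0.2 the change was −11%. With all 60 analysed, 10 prognostic candidates and |SMD| > 0.25, the true SE under the rule was 3% to 5% below that of the model with strata (for example 0.205 v 0.215).

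**The case against.** The strongest reply has four parts.

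- **The harm to precision is not established.** A reader might infer that the rule costs 14% to 27% in standard error, which is 1 − (0.245/0.280)² = 23% to 1 − (0.245/0.310)² = 38% of the information. Those figures need a threshold of 0.2, 13 to 20 candidates and covariates of no prognostic value, and the protocol states none of these. The PROGRESS-Plus factors are collected for description and are not named as candidates. Age, disability and socioeconomic status are unlikely to be noise for EQ-5D or costs. This part stands: the direction of the effect is not determined.
- **Selection uses baseline data.** A reader might take the clause as choosing covariates after seeing outcomes. The text refers to imbalance at randomisation, and nothing in it lets outcomes guide the choice. This also stands.
- **The article is condensed.** A full covariate list may sit in an analysis plan, which the steering committee is to agree, and the missing strata may be abbreviation. This stands only in part. The imbalance clause is a printed rule, and the same article found room to name the strata for weight.
- **The study is unpowered.** Expert elicitation and literature also feed the economic work, so a few per cent in one standard error reaches the trial decision weakly. This limits the weight of the point but does not make the rule a good one.

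**Conclusion.** The point holds in a limited form. Two parts rest on the text alone: the economic covariate set is left to chance imbalance with no stated criterion, and weight change has two adjustment sets in one protocol. That the rule in effect ignores the stratification follows from the stratified blocks, with the frequencies given under assumed block size and prevalence.

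The numerical consequence is modest and conditional. Omitting the strata overstates the reported standard error by about 4% to 18% for an assumed strata R² of 0.05 to 0.20, and by nothing if the strata are not prognostic. That overstatement reaches the cost-effectiveness probabilities if the bootstrap also ignores the strata. Imbalance selection can widen or narrow the true spread, depending on the threshold, the candidates and their prognostic value. The documents do not support a claim that the incremental estimates are biased, that type I error is inflated, or that a particular amount of precision is lost.

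The weight is moderate to low, because no comparison is powered. It is still worth correcting, since the study exists partly to quantify uncertainty and to test analytical methods for a full trial.

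**What to change.** In Economic analysis, replace the clause on unbalanced variables with a list fixed in advance:

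- QALYs: baseline EQ-5D-5L utility, diabetes status, sex.
- Costs: baseline cost, diabetes status, sex.
- Weight change: baseline weight, diabetes status, sex, which matches the Statistical analysis section.

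Any adjustment prompted by observed imbalance can be kept as a labelled sensitivity analysis.

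The cost is analysis wording only. All these variables are already collected at baseline, and neither the sample size nor the conduct of the study changes.

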**Methods and analysis:**

This is a pragmatic, randomised, single-blind, parallel group, two-arm, feasibility study with an embedded process evaluation. We will recruit and randomise 60 adults who have recently completed a behavioural weight loss programme to the ACT-based intervention or standard care, using a computer-generated sequence with 2:1 allocation stratified by diabetes status and sex. Baseline and 6-month measurements will be completed using online questionnaires. Qualitative interviews will be conducted with a subsample of participants and coaches about their experiences at 3 (mid-intervention) and 6 (postintervention) months. Feasibility and acceptability of the intervention, and a full-scale trial will be assessed using a number of outcomes, including adherence to, and engagement with the intervention, recruitment and retention rates, proportion of missing data for each outcome measure, participants’ experiences of the intervention and study, and coaches’ experiences of delivering intervention support. Quantitative and qualitative findings will be integrated and summarised to contribute to the interpretation of the main feasibility evaluation findings. Value of information methods will be used to estimate the decision uncertainty associated with the intervention’s cost-effectiveness and determine the value of a definitive trial.

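### The cost-effectiveness probability, defined as the share of bootstrap ICERs below the threshold, misclassifies replicates in which SWiM is less effective; net benefit should define it.

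*Protocol article*

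**What the plan says.** All of this is in the protocol article, under Data analysis.

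- Economic analysis defines the ICER as a signed ratio, "calculated by dividing the mean cost difference by the mean effectiveness difference".
- The same section says that uncertainty in incremental cost and effect "will be evaluated using non-parametric bootstrapping methods and presented as cost-effectiveness probabilities", and fixes the estimator: "estimated as the proportion of the bootstrapped cost and effectiveness pairs with corresponding ICERs below different values of the cost-effectiveness threshold".
- Two effect measures are used: "The outcomes used in the cost-effectiveness analysis will be the change in weight over time and HRQOL captured by the EuroQol EQ-5D-5L questionnaire", the latter expressed as QALYs.
- Statistical analysis, a separate section, estimates the "difference (intervention minus standard care) in mean change in weight from baseline". On that scale a benefit of SWiM is a negative number.
- The Economic analysis section has no rule for negative ICERs or dominated replicates, does not mention net benefit, and sets no sign for the weight effect.
- On value of information (VOI), it says that "the results of the probabilistic sensitivity analyses will be combined with the epidemiological information on projected numbers to undertake a VOI analysis".

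**The concern.** An ICER has no consistent ordering over the cost-effectiveness plane. A negative ratio can mean that SWiM is cheaper and better, or costlier and worse. A positive ratio below the threshold is good news when SWiM gains health and bad news when it loses health. Comparing the bare ratio with a threshold therefore works only on the half of the plane where the effect difference is positive.

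That half may not hold nearly all of the replicates here. The study randomises 60 people 2:1, follows them for 6 months, and says itself that it lacks power for group comparisons. SWiM adds a web platform and coach calls, whereas standard care is an emailed leaflet, so a higher cost for SWiM is plausible. The misclassified replicates would then be mostly dominated ones counted as cost-effective, and the reported probability would be too favourable to SWiM.

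**Working it through.** The plan states no figure for this probability, so there is none to reproduce.

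**1. The rule against net benefit.** Let ΔC and ΔE be the cost and effect differences (SWiM minus standard care, with larger effect better), λ the threshold, and NB = λΔE − ΔC.

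- If ΔE > 0, then ΔC/ΔE < λ is the same as ΔC < λΔE, that is NB > 0. The rules agree.
- If ΔE < 0, multiplying by ΔE flips the inequality: ΔC/ΔE < λ is the same as ΔC > λΔE, that is NB < 0. The rule counts a replicate exactly when it is not cost-effective.

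**2. Examples at λ = £20,000 per QALY.**

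| ΔC | ΔE (QALY) | ICER | Counted by the rule? | NB |
|---|---|---|---|---|
| +£100 | +0.01 | £10,000 | yes | 200 − 100 = +£100 |
| +£100 | −0.01 | −£10,000 | yes | −200 − 100 = −£300 |
| −£100 | −0.01 | £10,000 | yes | −200 + 100 = −£100 |
| −£300 | −0.01 | £30,000 | no | −200 + 300 = +£100 |

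The last three rows are all misclassified. This step needs no assumption about the trial's results.

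**3. Size: inputs.**

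- From the document: 60 randomised at 2:1, so about 40 and 20.
- Assumed: 80% follow-up (32 and 16); utility SD 0.2; correlation of 0.6 with baseline; area-under-curve weight 0.25; mean extra cost £150 with SE £100; cost and effect normal and uncorrelated; λ = £20,000.
- QALY SD after baseline adjustment: 0.25 × 0.2 × √(1 − 0.6²) = 0.04. QALY SE: 0.04 × √(1/32 + 1/16) ≈ 0.0122.

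**4. Size: formulas.**

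- SE of NB = √((20,000 × 0.0122)² + 100²) = √(244² + 100²) = £263.7.
- P(NB > 0) = Φ(mean NB / 263.7).
- From step 1, P(rule) = P(NB > 0) + P(ΔE < 0) − 2 × P(ΔE < 0 and NB > 0). The joint term comes from the bivariate normal distribution.

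| Mean ΔC | Mean ΔE | Mean NB | P(NB > 0) | P(ΔE < 0) | Joint term | P(rule) |
|---|---|---|---|---|---|---|
| +£150 | 0 | −£150 | 0.285 | 0.500 | 0.0047 | 0.775 |
| +£150 | 0.02 | +£250 | 0.828 | 0.051 | 0.0010 | 0.877 |
| +£150 | 0.03 | +£450 | 0.956 | 0.007 | 0.0002 | 0.963 |
| −£300 | 0 | +£300 | 0.872 | 0.500 | 0.3724 | 0.628 |

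The rule thus gives about 78% against 28%, 88% against 83%, and a difference of 0.7 points in the first three rows. In the last row, where SWiM saves £300, it gives about 63% against 87%, an understatement. At zero gain, extra cost £150 and a threshold near £0, the figures are 50% against Φ(−1.5) = 7%.

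**5. A second set of assumptions.** All 40 and 20 analysed; QALY SD 0.05 or 0.10; cost SD £300 or £1,000; QALY gain 0 to 0.02; extra cost £100 or £200; λ of £20,000 or £30,000. In all 64 scenarios the rule overstates, by 4 to 50 percentage points, and between 7% and 50% of replicates have ΔE < 0. All 64 assume that SWiM costs more.

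**6. Weight.** If the sign in Statistical analysis were carried over, a replicate costing £100 more with 1 kg of benefit would have ΔE = −1 and an ICER of −£100 per kg, which lies below any positive threshold however costly SWiM is. One with 1 kg of harm would have +£100 per kg.

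**The case against.** The strongest reply is that the sentence is shorthand. It speaks of cost and effect pairs, so dominated replicates remain identifiable, and a health economics plan that is not shown may handle the quadrants properly. That is possible, and it would be wrong to say that the investigators will certainly count dominated replicates. But the article does not leave the estimator open. It states one, and that one is wrong when followed literally.

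Three stronger readings are tempting and are not supported:

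- A reader might infer that the value-of-information work, and so the case for a definitive trial, is distorted. Statistical analysis bases the VOI on structured expert elicitation using feasibility data. Economic analysis feeds in probabilistic sensitivity results without saying that these proportions are among them. A rule for summarising replicates leaves the underlying cost and effect pairs unchanged. An effect on VOI is only a possibility.
- A reader might infer that the rule always overstates. It does so in the scenarios above where SWiM costs more, but understates in the one where SWiM saves £300.
- A reader might infer that the weight-based ICER is already reversed. Economic analysis sets no sign for weight, so this arises only if the other section's convention is carried over.

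It also stands that the gap nearly vanishes if the QALY gain is large relative to its SE, and that no progression criterion in the article depends on this probability.

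**Conclusion.** The estimator is wrong as written: it reverses the classification of every replicate with a negative effect difference, ties aside. That follows from algebra and does not depend on assumed figures. The size does. With an assumed extra cost of £150, the overstatement at £20,000 per QALY runs from about 50 points at zero QALY gain to under 1 point at a gain of 0.03. The direction rests on SWiM costing more than the leaflet, which is plausible but not stated as a figure. The matter is worth correcting because these probabilities are how the article presents economic uncertainty. It concerns a secondary output of a feasibility study and does not threaten the study's main aims.

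**What to change.** Replace the definition in Economic analysis with this: for each threshold, compute threshold × incremental effect − incremental cost in every bootstrap replicate, and report the proportion of replicates above zero. State that weight effectiveness is coded so that a larger value is better (kg lost or regain avoided). If a separate health economics plan already does this, align the wording with it.

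The cost is a sentence or two of text and a line of code, with no new data and no design change. The reported probabilities may move in either direction.
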